### Data Sources and Measurements

As mentioned above, for ANA, RF and ANCA measurements, all the samples will be centralized in the autoimmunity laboratory of the Central Laboratory of the Araba University Hospital (Vitoria-Gasteiz). The measurements will be carried out by two blinded technicians with accredited experience in the field of autoimmunity tests.

In accordance with current recommendations (Agmon-Levin et al., 2014), ANA detection will be performed using IFAs on a fully automated system (EUROPattern, EUROIMMUN), using a combination of HEp-2 cells and rodent tissue sections as a dual substrate. If IFA results are positive in one or more screening dilutions, the serum will be serially diluted and re-analyzed until fewer than half of the cells on the slide produce detectable fluorescence; the ANA titer will be reported as the dilution prior to the point at which this occurs. Antinuclear antibodies will be considered positive from a titer ≥1:40 on rodent tissue and ≥1:80 on HEp-2 cells. Positivity will be classified as low or high based on ANA titers between 1:40 and 1:160, and ≥1:320, respectively.

Quantitative measurement of RF will be performed on serum samples with the ARCHITECT automated analyzer (Abbott) (Dupuy et al., 2014), based on a latex agglutination immunoturbidimetry technique using an antigen-antibody reaction between RF present in the sample and denatured human immunoglobulin isotype G adsorbed on latex particles. The resulting agglutination is detected as a change in absorbance (572 nm), and the magnitude of the change is proportional to the amount of RF in the sample. The concentration is estimated by interpolation on a calibration curve prepared from calibrators of known concentration. The result will be considered positive if the RF value is greater than 30 IU/ml.

Testing of ANCAs will be performed using an IFA in a fully automated system (EUROPattern), and results will be considered positive for titers ≥ 1:20. Borderline and positive samples will be retested with myeloperoxidase and proteinase-3 immunoassays from Thermofisher® on the UNICAP 250 analyser using fluoroimmunoassay technology.

### Management of Potential Bias

The inclusion of patients with previous ADs could be influenced by attending physicians’ concern about inducing irAEs, and this could lead to a biased representation of the population eligible for the study. Researchers will encourage oncologists to include patients with ADs in remission on a case-by-case basis.

To minimize a detection bias arising from a higher level of suspicion of irAEs in autoantibody-positive patients, the autoantibody panel under study will be performed and the results analyzed after the whole cohort reaches week 48 of follow-up. On the other hand, for ethical and practical reasons, the autoantibody results from the extraordinary samples taken for medical purposes will be available to the attending physicians. Nonetheless, the laboratory staff involved in the detection and interpretation of autoantibodies will always be unaware of the clinical status of each patient.

### Sample Size Calculation and Statistical Analysis

To estimate an expected sensitivity of the autoantibody panel under study of 0.90 with a 95% confidence interval of not less than 0.75, 70 cases with irAEs will be needed. Considering irAEs associated with ICIs will develop in 25% of cases (Wang et al., 2019), a total of 210 patients without irAEs will be required. Considering a loss to follow-up of 5%, we should recruit a total of 294 patients.

Regarding the statistical analysis, firstly, a description of the cohort will be performed. Quantitative variables will be reported as mean ± standard deviation or median (interquartile range) and compared between groups using Student’s t-test for unpaired data or the Mann-Whitney U-test, depending on whether data follow a normal distribution. Categorical variables will be expressed as frequencies (percentages) and compared between groups using Pearson’s Χ^2^ or Fisher’s exact test based on the expected frequency of cells. To assess the primary endpoint of the study (i.e., proportion of patients developing at least an irAE), the autoantibody panel will be considered positive when any of the autoantibodies included in the panel is positive according to the following cut-off points: ANA titers ≥ 1:40, ANCA titers ≥ 1:20 or RF value ≥ 30 IU/ml. The autoantibody panel and the titers of autoantibodies will be handled as a categorical variable (namely, positive or negative result) and as a quantitative variable, respectively. It is planned to perform a subgroup analysis depending on whether or not patients have an AD before their inclusion. An analysis of variance for repeated measures will be performed to explore the profile of detectable autoantibodies over the 48 weeks of follow-up.

Survival will be assessed using a Kaplan-Meier analysis and compared between groups using the log-rank Mantel-Cox test. A subgroup analysis according to tumour type and extent of cancer (local, advanced, and metastatic disease) will be performed to assess survival outcomes*.* A multivariate analysis using logistic regression and Cox regression will be performed to detect factors associated with the occurrence of irAEs. Applying a manual backward stepwise procedure, a multivariate model will be constructed from variables that either have a p-value of less than 0.10 in the univariate analysis or are considered relevant to the dependent variable on the basis of previous studies (e.g., sex and age of patients, type of ICI). Variables not reaching statistical significance will be dropped from the final predictive model. The sensitivity, specificity, positive predictive value, negative predictive value, and probability ratios with their corresponding 95% confidence intervals of the model will be calculated. The diagnostic accuracy of the predictive model inferred from the logistic regression model will be described with the area under the receiver operating characteristic curve.

Two-sided hypothesis tests will be performed, and the significance level will be set at 5%. The statistical analysis will be conducted using IBM SPSS Statistics software version 27.0 (Chicago, IL).

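### Student's pooled t-test is fixed for groups planned at about 70 and 210; if their spread differs, its test of equal means misses the nominal level, and Welch's test would hold it almost for free (minor)

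*Protocol article*

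**What the plan says.** All the relevant text is in the protocol article, section Sample Size Calculation and Statistical Analysis.

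- **Test.** Quantitative variables are compared between groups with Student's "t-test for unpaired data or the Mann-Whitney U-test, depending on whether data follow a normal distribution". The article says nothing about unequal variance.
- **Group sizes.** "70 cases with irAEs will be needed", on the expectation that "irAEs associated with ICIs will develop in 25% of cases", so that "a total of 210 patients without irAEs will be required". The planned split is therefore 1:3.
- **Screen.** Two paragraphs describe the analysis. The second builds the multivariate model "from variables that either have a p-value of less than 0.10 in the univariate analysis", or that are judged relevant from earlier studies, with age, sex and type of ICI as examples. It does not name the test behind the univariate p-value. Logistic and Cox regression are mentioned just before.
- **Level.** Tests are two-sided at 5%.

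**The concern.** Checking normality does not check what Student's test also needs, which is equal variances. Normal data can have unequal spread. With equal group sizes this hardly matters, because the pooled standard error is then right on average. With a 1:3 split it matters, because the pooled variance is dominated by the larger group:

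- If the smaller irAE group is more variable, the standard error is too small and the test rejects too often.
- If the irAE group is less variable, the standard error is too large and the test rejects too rarely.

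At stake are the p-values for normally distributed quantitative variables in the irAE versus no-irAE comparisons. Candidates could include body mass index or haemoglobin from the Variables section. If the screen uses the same tests, it is also at stake which of these variables reach the model.

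**Working it through.** **1. The plan's own figures.** 70/0.25 = 280 in total, and 280 − 70 = 210 without irAE. Adding 5% gives 280 × 1.05 = 294, as stated. (Dividing by 0.95 would give 295; the difference is immaterial here.) The group sizes n1 = 70 and n2 = 210 are thus the plan's own.

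**2. Formula.** Let r be the SD in the irAE group divided by the SD in the no-irAE group, the latter set to 1. The article gives no SDs, so r is an assumption, shown over a range.

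- True variance of the mean difference: V = r²/70 + 1/210
- Variance that Student's test uses, on average: P = [(69r² + 209)/278] × (1/70 + 1/210)
- True two-sided error ≈ 2 × [1 − Φ(z × √(P/V))], with z = 1.96 at nominal 5% and 1.645 at nominal 10%

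**3. Numbers for r = 1.5.** V = 2.25/70 + 1/210 = 0.03690. P = (364.25/278) × 0.019048 = 0.02496. √(P/V) = 0.822. At nominal 5%, 1.96 × 0.822 = 1.612, so the error is 10.7%. At nominal 10%, 1.645 × 0.822 = 1.353, so the error is 17.6%.

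**4. Numbers for r = 0.667.** V = 0.4449/70 + 1/210 = 0.01112. P = (239.70/278) × 0.019048 = 0.01642. √(P/V) = 1.215. At nominal 5%, 1.96 × 1.215 = 2.382, so the error is 1.7%. At nominal 10% it is 4.6%.

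**5. Check by simulation** (200,000 runs, normal data, equal means, 70 versus 210):

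| r | Student, nominal 5% | Student, nominal 10% | Welch, nominal 5% | Welch, nominal 10% |
|---|---|---|---|---|
| 0.5 | 0.8% | 2.6% | 5.0% | 10.0% |
| 0.667 | 1.7% | 4.5% | 4.9% | 9.9% |
| 0.9 | 3.9% | 8.3% | 5.0% | 10.0% |
| 1 | 5.0% | 10.0% | 5.0% | 10.0% |
| 1.1 | 6.2% | 11.6% | 4.9% | 9.9% |
| 1.5 | 10.6% | 17.6% | 5.0% | 10.0% |
| 2 | 15.0% | 22.7% | 5.0% | 10.0% |

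With 140 versus 140, Student's test stays at 5.0% and 10.0% for r = 0.5 and r = 2. The cause is the 1:3 split combined with unequal spread, not unequal spread alone.

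**6. Lost power.** Take a true mean difference of 0.25 SD of the no-irAE group and r = 0.667. The chance of p<0.05 is 0.49 with Student and 0.65 with Welch; the chance of p<0.10 is 0.64 and 0.76. At r = 1 the two tests practically agree: 0.440 and 0.437 at 5%, 0.566 and 0.564 at 10%.

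**7. Other tests under the same conditions, nominal 10%** (3,000 runs, so approximate). Mann-Whitney rejects in about 5% of runs at r = 0.5 and 17% at r = 2. The Wald test from univariable logistic regression rejects in about 2% and 23%.

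**The case against.** **A variable unrelated to irAEs is safe.** A reader might infer from the table that noise variables would enter the model too often. The documents do not support that. A variable with no relation to irAEs has the same distribution in both groups, so r = 1 and Student's test holds its level whatever the split. The inflated figures need a variable whose means agree while its spread differs by irAE status, and such a variable is not pure noise. This objection stands. What remains is a false claim about means for such variables, and lost power in the other direction.

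**The link to the screen is not stated.** A reader might also infer that the p<0.10 screen is distorted as a matter of course. The t-test sentence belongs to the description of the cohort, which does not define the groups as irAE versus no irAE. The univariate analysis may equally be univariable logistic or Cox regression. This also stands. The two-group tests are the only ones named for quantitative variables, but that is an inference.

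**Few results are exposed.** Only quantitative variables judged normal go to the t-test. The panel result is handled as positive or negative, so its sensitivity estimate is untouched. Age, sex and type of ICI can enter without passing the screen. Backward elimination may remove a variable wrongly admitted, though it cannot recover one that was lost. All of this stands and limits the importance of the point.

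**The size is assumed.** No SDs are given, and the 1:3 split is an expectation. The pilot study described in the Discussion had 37.5% with irAEs. Applied to 280 patients, that is 105 versus 175, and at r = 1.5 the error at nominal 10% would be about 13.5% rather than 17.6%. The distortion shrinks but does not vanish.

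**It is a detail for the full analysis plan.** This does not stand in full. The article names Student's test and gives the rule for choosing it, so this is a stated choice and not a silence. If an unseen plan already specifies the unequal-variance form, only the wording here needs to follow.

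**Conclusion.** The point holds as a minor, nearly free improvement to the two-group comparisons. With planned groups of about 70 and 210, Student's t-test holds its nominal level only if spread is similar. At SD ratios of 1.5 and 0.67 the true error is about 10.7% and 1.7% at nominal 5%. Between 0.9 and 1.1 it lies between 3.9% and 6.2%, which few would worry about. These figures assume normal data, the planned split and the stated ratios; the article neither gives nor excludes any particular ratio.

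Any effect on the choice of predictors is conditional on the screen being run with these tests. The point does not call into question the panel's sensitivity or the sample size.

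**What to change.** In Sample Size Calculation and Statistical Analysis, replace Student's t-test by Welch's unequal-variance t-test for two-group comparisons of approximately normal variables. Use it also for the p<0.10 screen wherever that screen relies on a two-group t-test.

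The cost is a change of wording and a negligible loss of power at equal variances (0.437 against 0.440 in the example above). No extra patients or data are needed. The change does not repair p-values from Mann-Whitney or from univariable regression, which show a distortion in the same directions when spread differs.

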## Abstract

**Introduction:** Immune checkpoint inhibitor (ICI) therapy is markedly improving the prognosis of patients with several types of cancer. On the other hand, the growth in the use of these drugs in oncology is associated with an increase in multiple immune-related adverse events (irAEs), whose optimal prevention and management remain unclear. In this context, there is a need for reliable and validated biomarkers to predict the occurrence of irAEs in patients treated with ICIs. Thus, the main objective of this study is to evaluate the diagnostic performance of a sensitive routinely available panel of autoantibodies consisting of antinuclear antibodies, rheumatoid factor, and antineutrophil cytoplasmic antibodies to identify patients at risk of developing irAEs.

**Methods and Analysis:** A multicenter, prospective, observational, cohort study has been designed to be conducted in patients diagnosed with cancer amenable to ICI therapy. Considering the percentage of ICI-induced irAEs to be 25% and a loss to follow-up of 5%, it has been estimated that a sample size of 294 patients is required to detect an expected sensitivity of the autoantibody panel under study of 0.90 with a confidence interval (95%) of no less than 0.75. For 48 weeks, patients will be monitored through the oncology outpatient clinics of five hospitals in Spain. Immune-related adverse events will be defined and categorized according to CTCAE v. 5.0. All the patients will undergo ordinary blood tests at specific moments predefined per protocol and extraordinary blood tests at the time of any irAE being detected. Ordinary and extraordinary samples will be frozen and stored in the biobank until analysis in the same autoimmunity laboratory when the whole cohort reaches week 48. A predictive model of irAEs will be constructed with potential risk factors of immune-related toxicity including the autoantibody panel under study.

**Ethics and Dissemination:** This protocol was reviewed and approved by the Ethical Committee of the Basque Country and the Spanish Agency of Medicines and Medical Devices. Informed consent will be obtained from all participants before their enrollment. The authors declare that the results will be submitted to an international peer-reviewed journal for their prompt dissemination.

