#### Extraordinary samples

At the time an irAE is detected, an additional blood sample will be collected for tests including the autoantibody panel under study. At the discretion of the attending physician, screening for other more specific antibodies may be requested based on the clinical manifestations of the patient. For ethical and decision-making reasons, the results of these extraordinary analyses for medical purposes will be available to the attending physicians.

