### Laboratory Management and Sample Circuit

Both ordinary and extraordinary samples for research purposes will be separated from samples for medical purposes and will be processed to obtain six 500-μL aliquots of serum each. These aliquots will be stored at −80°C and appropriately labelled and coded in the biobank of each participating center. Ordinary samples corresponding to baseline (week 0), week 24 and week 48 will be processed to obtain peripheral blood mononuclear cells (PBMCs), which will be stored in the biobank at −80°C as cell pellets for subsequent DNA and RNA extraction.

After completion of follow-up, serum samples will be centralized in a single autoimmunity laboratory located in the Central Laboratory of Araba University Hospital (Vitoria-Gasteiz) to be analyzed by a blinded team of physicians and technicians with extensive experience in clinical laboratory testing. The panel of autoantibodies under study (ANAs, RF, and ANCAs) will be used to screen the serum from the ordinary and extraordinary samples. In some cases, the serum from the extraordinary samples obtained at the time of an irAE diagnosis may be tested for other more specific autoantibodies, at the discretion of the attending physician. In addition, vitamin D levels will be measured as 25-hydroxycholecalciferol in the serum from ordinary samples at baseline and weeks 24 and 48.

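### Panel positivity is not tied to a sample drawn before the irAE, so results obtained at or after the event may count as predicting it

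*Protocol article*

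**What the plan says.** The Abstract gives the panel's purpose as "to identify patients at risk of developing irAEs". Under Sample Size Calculation and Statistical Analysis, the rule that serves the primary endpoint is that "the autoantibody panel will be considered positive when any of the autoantibodies included in the panel is positive according to the following cut-off points". Cut-offs for ANA, ANCA and RF follow, with no mention of which sample or week is meant.

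Other sections set out which samples exist:

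- Ordinary Samples and Study Schedules: a week-0 sample and six later draws up to week 48. Ordinary sampling continues once treatment resumes after a delay caused by an irAE.
- Extraordinary samples: "At the time an irAE is detected, an additional blood sample will be collected for tests including the autoantibody panel under study".
- Laboratory Management and Sample Circuit: "The panel of autoantibodies under study (ANAs, RF, and ANCAs) will be used to screen the serum from the ordinary and extraordinary samples".
- Variables: autoantibody levels in ordinary and in extraordinary samples both appear under the independent variables, introduced as potential predictors of irAEs.

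Time limits appear only under Secondary Objectives. One comparison separates positivity before ICI initiation from positivity after it, and another objective follows autoantibodies up to irAE diagnosis. Neither limit is carried over to the panel rule or to the logistic model.

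**The concern.** A test that predicts an event has to be read before the event. Read together, these sections leave open a definition in which a patient is panel-positive if any sample is positive at any time. Two problems follow.

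1. **Order in time.** An autoantibody that appears with the irAE, or as a consequence of it, would be credited as having predicted it. The Discussion itself describes ways in which ICI treatment could release autoantibodies, such as tissue damage or cytokines, so antibodies arising alongside toxicity are plausible on the article's own account.
2. **Unequal testing.** Patients with an irAE get a draw that patients without one never get.

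What is at stake is the meaning of the headline sensitivity, and of the predictive model that the article plans to take to external validation. The safeguards under Management of Potential Bias (late batch testing, blinded laboratory staff) address detection bias. They do not address whether the sample came before the event.

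**Working it through.** **The plan's own figure.** The target is an "expected sensitivity of the autoantibody panel under study of 0.90 with a 95% confidence interval of not less than 0.75", for which "70 cases with irAEs will be needed". Exact binomial limits reproduce 70 under two conventions when the true sensitivity is 0.90:

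- two-sided 95% lower limit of at least 0.75, met with at least 60/70 positive, probability 0.913;
- one-sided 95% lower limit of at least 0.75, met with at least 59/70 positive, probability 0.956.

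For the total, "Considering irAEs associated with ICIs will develop in 25% of cases" gives 70/0.25 = 280. Then 280 − 70 = 210, as stated ("a total of 210 patients without irAEs will be required"), and 280 × 1.05 = 294. The arithmetic is sound. What is open is which sample the 0.90 describes.

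**Direction.** Under an any-positive rule, adding samples can turn a negative patient positive but never the reverse. Counting samples drawn at or after the irAE therefore cannot lower sensitivity, and raises it whenever a case converts then.

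**Illustration of size (assumed rates).** Take a panel with no predictive value. Let *b* be positivity at week 0, equal in cases and non-cases, and *e* the share of still-negative cases that turn positive only at the irAE.

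Apparent sensitivity = *b* + (1 − *b*) × *e*; specificity = 1 − *b*.

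| *b* | *e* | Sensitivity, week 0 | Sensitivity, irAE sample counted | Specificity | Youden index |
|---|---|---|---|---|---|
| 0.30 | 0.192 | 0.30 | 0.30 + 0.70 × 0.192 = 0.43 | 0.70 | 0.13 |
| 0.30 | 0.50 | 0.30 | 0.65 | 0.70 | 0.35 |
| 0.30 | 0.80 | 0.30 | 0.86 | 0.70 | 0.56 |
| 0.15 | 0.192 | 0.15 | 0.31 | 0.85 | 0.16 |

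In the first row, about 21 of 70 positive cases become about 30 of 70. The true Youden index is 0 in every row. The 30% is borrowed from the pilot's patients without irAEs, and the 19.2% from the seroconversion reported for a melanoma cohort. Neither is a known rate for this panel at these times.

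**The extra draw alone.** Suppose the irAE drives no conversion, and each later draw has the same background chance *q* of a new positive. With *b* = 0.30, cases have eight draws (seven ordinary plus one) and non-cases seven:

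- *q* = 2%: sensitivity goes from 1 − 0.70 × 0.98⁶ = 0.380 to 1 − 0.70 × 0.98⁷ = 0.392; specificity is 0.70 × 0.98⁶ = 0.62.
- *q* = 5%: sensitivity goes from 0.485 to 0.511; specificity is 0.70 × 0.95⁶ = 0.515.

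The additional draw is thus worth only 1 to 3 points. Repeated ordinary testing lowers specificity from 0.70 to about 0.62 or 0.52. A large artefact needs conversion driven by the irAE itself.

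**An upper check.** For a useless panel with *b* = 0.30 to reach 0.90 by this route, *e* would have to be 1 − 0.10/0.70 = 0.86.

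**The case against.** The strongest reply is that the positivity rule combines antibody types, not samples or times, and does not itself say that the extraordinary sample counts. The laboratory section says which serum is tested, not which result enters the accuracy table. The list under Variables also holds date of death and overall survival, so it is not a model specification. Because the article is condensed, the index sample may be named in a fuller document.

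Much of this stands. A reader might infer that the plan definitely counts the irAE-day sample and that sensitivity is therefore inflated. The article does not say so. Nor does Table 1 confirm it: its column records which antibody status is assessed, and the secondary objectives need both pre-existing and newly developed antibodies in any case.

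A reader might also infer an artefact of some 35 points. With 30% positive at baseline, that needs half of the remaining cases to convert because of the irAE, and the article gives no source for such a rate. The borrowed rates are weak too. The pilot is described as covering pre-existing and developed antibodies, so its 30% is not shown to be a baseline rate, and its battery is said in the Discussion to have included anti-thyroid antibodies. The 19.2% comes from a different and broader battery and is the upper figure for some antibody types.

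Finally, antibodies that appear on treatment but before an irAE can legitimately signal risk, and the study's hypothesis depends on them. They should not be discarded.

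What does not stand is that this is only detail left for later. The article fixes the positivity rule, the samples tested and the list of potential predictors, and together these admit a sample triggered by the outcome. No passage excludes it.

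**Conclusion.** The point holds in conditional form. As written, nothing stops results obtained at or after an irAE from counting as predicting it. If they count, the upward direction for sensitivity is certain, and repeated testing lowers specificity, so not every accuracy measure is biased the same way. The size is unknown: 0.30 to 0.43 is an illustration resting on two assumed rates, and without irAE-driven conversion the artefact is only a few points. Whatever its size, figures computed that way would not answer the stated question of who is at risk. This should be settled in the text before the stored samples are analysed.

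**What to change.** Under Sample Size Calculation and Statistical Analysis:

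1. Compute sensitivity, specificity, predictive values, likelihood ratios and the logistic model (with its ROC curve) from the week-0 panel, and state that the 0.90 expectation and 0.75 lower limit refer to that sample.
2. Analyse on-treatment positivity only as a time-updated covariate in the Cox model, using samples drawn before irAE onset. This preserves the seroconversion hypothesis.
3. Use extraordinary and post-irAE samples for description only.
4. Treat other repeatedly measured laboratory predictors the same way. For example, vitamin D at weeks 24 and 48 should not enter the fixed-time model.

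The essential element is barring samples drawn at or after irAE onset from the accuracy measures and models. Week 0 is the clean choice for the fixed-time measures because every patient has it at the same point.

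The cost is wording: the week-0 samples are already scheduled, and the 70/280/294 arithmetic does not change. The downside is that the reported sensitivity may be lower than under any-time positivity.
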